## Abstract

**Background:**

Post-stroke depression (PSD) is the most common mental complication after stroke and has a serious impact on functional outcomes and quality of life for stroke patients. Antidepressants are the first-line treatment for PSD; however, many reported side effects remain. Clinical research and practice guidelines have shown that electro-acupuncture (EA) or rTMS have a positive effect on PSD. However, there are few clinical studies on EA and MRI-navigated rTMS for PSD that explore the fMRI-based central mechanism in depression.

**Methods:**

In this randomized, controlled, open-label trial, 64 patients with PSD will be randomly allocated into the experiment group (*n* = 32) or control group (*n* = 32). The experiment group will receive EA and MRI-navigated rTMS and the control group will receive MRI-navigated rTMS treatment, in 12–20 sessions over 4 weeks. In addition, 10 healthy people for fMRI scanning will be recruited as a healthy control group without any intervention. The primary outcome will be the change from baseline in the Hamilton Depression Scale-24 item (HAMD-24) scores at week 4. The primary analysis of the central mechanism will mainly involve cortical morphology, local spontaneous brain activity, and the default mode network (DMN) functional connectivity based on fMRI at 0 and 4 weeks. Secondary outcomes will include the neuro-patho-physiological and quality of life changes in cortical excitability, determined using the motor evoked potential test (MEP), National Institutes of Health Stroke Scale (NIHSS), EuroQol Five Dimensions Questionnaire (EQ-5D) Scale, Modified Barthel Index (MBI) Scale, and Health Scale of Traditional Chinese Medicine (HSTCM). Additional indicators will include the Acceptability Questionnaire and Health Economics Evaluation (cost-effectiveness analysis) to assess the acceptability and economic practicality of the treatment under study. Outcomes will be assessed at baseline and post intervention.

**Discussion:**

EA and MRI-navigated rTMS therapy could become an alternative treatment for PSD, and it is expected that this trial will provide reliable clinical evidence and a potential central mechanism for the future use of EA and MRI-navigated rTMS for PSD.

**Clinical trial registration:**

NCT05516680, ClinicalTrials.gov (registered in August 2022).

## Introduction

Post-stroke depression (PSD), characterized by hopelessness and loss of interest, is a common emotional complication after stroke. Approximately one-third of stroke patients will suffer from depression (1). It has been reported that the incidence of PSD is 4 to 10 times in the common population (2). PSD increases the risk of stroke recurrence/mortality (3) and harms stroke recovery and quality of life (4). In particular, during the COVID-19 pandemic, depression symptoms in patients with stroke increased (5). As we know, PSD is directly related to stroke; however, its underlying mechanisms remain unclear. Moreover, the diagnosis of PSD is mainly assessed using scales, which lack in objective indicators. In addition, because of aphasia and cognitive impairment in stroke patients (6, 7), it is difficult to determine changes in interest and emotion, which makes the early diagnosis and therapy of PSD incredibly challenging. Therefore, it is critical to seek positive and stable predictors for PSD.

Currently, there is still a lack of long-term, safe, and effective therapy for PSD. Based on treatment guidelines for primary depression, anti-depressants are still the clinical first-line therapy for PSD. However, anti-depressants fail to work in approximately 40 to 60% of depressed patients (8), and their onset of effect is usually delayed by 2 to 4 weeks (9). Moreover, several anti-depressants have a risk for cerebrovascular and cardiovascular diseases, leading to low compliance with pharmacological treatment (10). Hence, the need for a safe and effective non-pharmaceutical anti-depression strategy is urgent to prevent depression in patients with stroke.

Acupuncture is a typical, promising, and traditional non-drug therapy, which has been widely used in the treatment of stroke-related diseases in China. Acupuncture, as a national heritage of China, has been recommended for PSD in many international guidelines (11, 12). A network meta-analysis of acupuncture has revealed that, as an adjunctive therapy, it is effective and safety for improving depression in stroke survivors and, combined with repetitive transcranial magnetic stimulation (rTMS), would be a better strategy, with the highest probability (13). The American FDA has approved rTMS as a non-invasive physiotherapy technique, and it is one of the commonly used neuroregulatory techniques for depression in the world. It is reported that publicly funding rTMS for adults with treatment-resistant depression in Ontario over the next 5 years would add $63.2 million in total costs (14). A meta-analysis has shown that patients with PSD may benefit from rTMS (15). Moreover, stroke survivors with depression had positive attitudes toward rTMS (16). rTMS delivers magnetic pulses to stimulate the areas of the brain associated with mood regulation. However, the efficacy of rTMS can be greatly affected by the precise position of the rTMS coil on the scalp (17). In terms of therapeutic target selection, high-frequency rTMS in the left dorso-lateral prefrontal cortex (DLPFC) is often recommended in guidelines to treat PSD (18). However, clinical rTMS typically uses scalp-based landmarks for DLPFC targeting (the ‘5-cm rule’), which cannot achieve accurate positioning because of anatomical differences between individuals. In this study, an alternative method of individual anatomical MRI-guided neuronavigation will be used to accurately locate the DLPFC, so as to realize the focusing and individualization of rTMS targeting. Therefore, acupuncture and rTMS may be a promising choice for PSD.

Few studies have investigated the therapeutic efficacy of acupuncture combined with rTMS, let alone electro-acupuncture (EA) and MRI-navigated rTMS. In addition, the therapeutic central mechanism remains unclear. Existing studies on PSD associated with certain neuro-imaging biomarkers have used resting-state functional MRI (rs-fMRI) based on blood-oxygen-level-dependent (BOLD) signals, and this is a popular and promising method to demonstrate the interactions of brain networks for PSD (19–21). To the best of our knowledge, stroke is often characterized by many changes in the functional connectivity (FC) of neural networks in the brain, which mostly lead to an abnormal emotional circuit, such as the default mode network (DMN) (20). In particular, the DLPFC plays a vital role in the emotional regulation of PSD. Thus, based on rs-fMRI studies, it can help to provide the neuromechanisms and potential targets of the clinical response to EA and MRI-navigated rTMS, building objective criteria to evaluate the therapeutic benefit. In addition, independent component analysis (ICA) will be utilized to assess FC alterations in the DMN, based on the spontaneous low-frequency oscillations (LFOs) of BOLD-fMRI signals representing the brain’s neural networks.

Above all, a randomized, controlled, open-label trial has been designed to investigate the efficacy and central mechanism of EA and MRI-navigated rTMS for PSD by using depression scales and rs-fMRI measurements. Moreover, the improvement of the activities of daily living (ADLs) function of PSD will be also evaluated using related scales.

## Methods

### Design

A single-center, randomized, controlled, open-label trial will be performed at Nanjing Drum Tower Hospital, The Affiliated Hospital of Nanjing University Medical School (Nanjing, China). All 64 participants will be randomized into the experimental group (EA and MRI-navigated rTMS) or the control group (MRI-navigated rTMS) at a ratio of 1 to 1. All patients in the two parallel groups will be treated over 12 ~ 20 sessions for 4 weeks (3 ~ 5 sessions per week). The clinical protocol items conform to the SPIRIT 2013 statement (22) and the Revised Standards for Reporting Interventions in Clinical Trials of Acupuncture (STRICTA) (23). The SPIRIT checklist has been presented. The study procedure is listed in Figure 1, and the study schedule is summarized in Table 1.

**Figure 1 fig1:**
[figure not shown]
Participant flowchart.

**Table 1 tab1:** Schedule of enrollment, interventions, and assessments.

Study procedure	Study period	
	Enrolment (d)	Treatment period (d)
Time-points	-5th-0d	28th ± 5d
Enrolment		
Demographics	X	
Vital signs	X	
Medical history	X	
Complications	X	
Eligibility screen	X	
MEPs	X	
GCS	X	
NIHSS	X	
HAMD-24	X	
Informed consent	X	
Random allocation	X	
Interventions		
Acu + rTMS	X	
rTMS	X	
Assessments		
rs-fMRI	X	X
HAMD-24	X	X
MEPs	X	X
NIHSS	X	X
MBI	X	X
EQ-5D	X	X
SF-HSTCM	X	X
Acceptability questionnaire		X
Safety evaluations	X	
Patient compliance	X	
Drug combinations	X	
Adverse events	X	
Research summary	X	
Review statements	X	

### Subjects

#### Recruitment strategies

This study will be carried out at the Nanjing Drum Tower Hospital, The Affiliated Hospital of Nanjing University Medical School. All participants will be recruited from the department of TCM, the department of neurology, or the department of psychology. Three doctors ([name], [name], and [name]) will help to recruit patients and healthy participants from three departments. Recruiting posters and a WeChat platform will be also adopted to collect cases.

### Inclusion criteria

(1) Inclusion criteria for patients include the following:Meet the diagnostic criteria for first onset stroke within 6 months, based on the Chinese Guidelines for Diagnosis and Treatment of Acute Ischemic Stroke 2018 (24).Aged 40–75 years.Right-handed.Single infarct in basal ganglia (volume: 3–5 cm).Motor evoked potential (MEP) could be recorded by bilateral primary motor cortex (M1) stimulation.National Institutes of Health Stroke Scale (NIHSS) score < 6.Hamilton Depression Scale-24 items (HAMD-24) score > 8.Clear consciousness, no hearing and visual impairment, and cooperative physical examination (Glasgow Coma Scale (GCS) score > 8).Complete the screening and voluntarily sign the informed consent form.(2) Inclusion criteria for healthy subjects include the following:Healthy subjects, aged 40–75 years.Right-handed.HAMD-24 score < 8.Voluntarily sign the informed consent form.

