### Sample size

Sample size was calculated based on the literature change of HAMD-24 scores as a primary outcome measure, using the following formula for a comparison between the two groups:

$$n_{2}=\frac{k+1}{k}\frac{{\left(Z_{\alpha /2}+Z_{\beta }\right)}^{2}\sigma^{2}}{\delta^{2}}$$

$$n_{1}=kn_{2}$$

A two-sample *t* test was selected in this research; σ represents the difference between the standard deviations of the HAMD-24 scores at 4 weeks in the experimental group (EA + rTMS) and the control group (rTMS) and δ indicates the difference between the means of the HAMD-24 scores in the two groups. G·Power software (version 3.1.9.7) was used for sample size calculation. According to the results from existing published literature (29), the mean (standard deviation) of the HAMD-24 at baseline before treatment was 27.52 (2.06) for the experimental group and 27.84 (2.55) for the control group. The mean (standard deviation) of the HAMD-24 after 4 weeks of treatment was 11.06 (3.37) for the experimental group and 14.13 (3.15) for the control group. To achieve a power (1 − β) of 0.90 at an alpha level of 5% (2-tailed) and a k value of 1, it was estimated that approximately 25 individuals will be needed in each group. Anticipating a 20% drop-out rate, a total of 64 subjects will be recruited to take part in the study, with 32 patients in each group. Moreover, 10 healthy subjects will be involved in the study, from which normal MRI data will be collected, without randomization and intervention.

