### Randomization and allocation concealment

Eligible patients who meet the criteria will be randomly assigned to the experimental or control group at a ratio of 1 to 1, with a randomized block design, namely, A and B. Independent random sequences will be computer-generated and retained by the principal investigator (PI) ([name]), who will not be involved in outcome measurement or data analysis. Therapists will receive each subject’s random number and group assignment through consecutive opaque envelopes. Before participation, the subjects will be informed that they have an equal opportunity to be allocated in either the experimental or control group.

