### Statistical analysis

All data analyses of this study will be done by an independent statistician ([name]) from University of Cape Town in South Africa using IBM SPSS Statistics for Windows, version 25.0 (IBMCorp., Armonk, N.Y., USA). The modified intention to treat (mITT) principle will be applied for all outcomes in the full analysis set. If the endpoints are missing, the last-observation-carried-forward (LOCF) method will be used according to mITT analysis. The mean, standard deviation (SD), minimum (min), maximum (max), and median will be reported for the quantitation data. The frequency (*n*) and corresponding percentage (%) will be given for the enumeration data. For intra-group comparisons, Student’s paired t test or Wilcoxon signed rank test will be used, and the chi-squared test will be utilized for qualitative indexes. For inter-group comparisons, independent-sample T test or Mann–Whitney U test will be applied. Pearson correlation coefficient or Spearman correlation coefficient will be used for correlation analysis between scale scores and fMRI data. An alpha level of 5% (2-tailed) will be selected.

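### Time since stroke, open from 0 to 6 months, is neither a named stratification factor nor a covariate, so any prognostic effect it has costs precision that one prespecified covariate would recover

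*Protocol article*

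**What the plan says.** Under Inclusion criteria, the protocol article requires "first onset stroke within 6 months". That is an upper limit only; neither the inclusion nor the exclusion list sets a minimum interval.

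Under Randomization and allocation concealment, allocation is 1:1 "with a randomized block design, namely, A and B". A and B are the arm labels, as the Blinding section confirms. No stratification factor is named.

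Under Statistical analysis: "For inter-group comparisons, independent-sample T test or Mann–Whitney U test will be applied". The Sample size section agrees for HAMD-24: "A two-sample *t* test was selected in this research". Neither test carries a covariate.

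Time since stroke does not appear as a factor, covariate, subgroup or limitation. The limitations in the Discussion mention infarct region as a possible influence on rs-fMRI, but not the stage of recovery.

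**The concern.** Patients at different intervals after stroke may change differently over the same four weeks, whatever the treatment. If so, time since stroke is a baseline prognostic factor that neither the described design nor the described analysis uses. Two things follow. Its contribution to the outcome stays in the error term and widens the confidence interval. And in a trial of 32 per arm, the arms can differ in it by chance, with nothing in the analysis to correct the estimate for the difference actually seen.

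The outcomes open to this are HAMD-24, NIHSS, MBI, MEP and the rs-fMRI measures. At stake is efficiency in a trial planned on 25 completers per arm. The remedy needs only a date that has to be known to check the six-month criterion.

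**Working it through.** **Inputs from the Sample size section.** Week-4 HAMD-24 mean (SD) is "11.06 (3.37) for the experimental group and 14.13 (3.15) for the control group"; "To achieve a power (1 − β) of 0.90"; "an alpha level of 5% (2-tailed) and a k value of 1"; 25 per group before and 32 after a 20% drop-out allowance.

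**Inputs not in the protocol, taken as assumptions.** The share R² of week-4 HAMD-24 variance explained by time since stroke, range 0 to 0.30. The distribution of time since stroke, uniform over 0–6 months.

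**1. Reproduce the plan's figure.** Difference δ = 14.13 − 11.06 = 3.07. Pooled SD σ = √[(3.37² + 3.15²)/2] = 3.26. Standardised difference = 3.07/3.26 = 0.94. The normal-approximation formula gives 24 per group; the two-sample t test (noncentral t) gives 25, with power 0.903. Then 25/0.8 = 31.25, so 32 per group and 64 in total. The stated sample size is correct.

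**2. How far the arms may differ by chance.** SD of a uniform 0–6 month time = 6/√12 = 1.73 months. SE of the arm difference in means = 1.73 × √(2/n).

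| Per arm | SE (months) | 95% range | P(gap > 0.5 month) | P(gap > 1 month) |
|---|---|---|---|---|
| 32 | 0.43 | ±0.85 | 25% | 2% |
| 25 | 0.49 | ±0.96 | 31% | 4% |

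If instead half the patients are early-stage, the exact chance with 32 per arm that the early share differs by more than 12.5 percentage points is 21% (exactly 32 of 64 early, hypergeometric) or 26% (independent binomials). Moderate imbalance is plausible; large imbalance is not common.

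**3. Effect on power for HAMD-24.** There are two scenarios, because the protocol does not say how widely time since stroke varied in the planning study.

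- Scenario A: the variance is already inside σ = 3.26. Unadjusted power stays at 0.90. Adjustment lowers the residual SD to σ√(1 − R²).
- Scenario B: the variance comes on top. The unadjusted SD becomes σ/√(1 − R²), and adjustment brings it back to 3.26 and power to 0.90.

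| R² | A: adjusted SD | A: adjusted power, 25/arm | B: unadjusted SD | B: unadjusted power, 25/arm | B: unadjusted power, 32/arm |
|---|---|---|---|---|---|
| 0 | 3.26 | 0.90 | 3.26 | 0.90 | 0.96 |
| 0.05 | 3.18 | 0.92 | 3.35 | 0.89 | 0.95 |
| 0.10 | 3.09 | 0.93 | 3.44 | 0.87 | 0.94 |
| 0.20 | 2.92 | 0.95 | 3.65 | 0.83 | 0.91 |
| 0.30 | 2.73 | 0.97 | 3.90 | 0.78 | 0.87 |

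Taking off one degree of freedom for the covariate changes these powers by less than 0.001. Any gain from baseline HAMD-24 is not counted.

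**4. Shift of the estimate by chance imbalance.** In scenario B with 25 per arm, the 95% range of the shift is ±1.96 × √R² × SD × √(2/25). For R² = 0.05 this is ±1.96 × 0.224 × 3.35 × 0.283 = ±0.4 points; for R² = 0.30, ±1.96 × 0.548 × 3.90 × 0.283 = ±1.2 points. The planned difference is 3.07.

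**5. Validity.** In a simulation of 40,000 trials with R² = 0.20 and 25 per arm, the unadjusted t test rejected a true null hypothesis in 5.0% of trials.

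**The case against.** The strongest reply is that nothing here is invalid. Randomisation balances time since stroke on average, and the standard error of the unadjusted test already allows for chance imbalance. The eligibility rules narrow the population in other ways: a single basal ganglia infarct, NIHSS below 6, MEPs recordable on both sides, no aphasia. Time since stroke is one of several possible covariates, and a full protocol or SAP may name some. All of this stands, except that the article does more than stay silent: it names tests that cannot carry a covariate.

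Several stronger readings are tempting, and the protocol does not support them.

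- *Power is below the stated 90%.* That would follow if the planning study had enrolled a narrow range of times since stroke. The Sample size section gives only its means and SDs. Under scenario A there is no shortfall.
- *Power falls to about two thirds.* A figure of 67% with 25 per arm needs early and late patients to differ by 6 points: SD = √(3.26² + 3²) = 4.43, with time explaining 9/19.64 = 46% of the variance. No figure in the protocol supports so strong an effect. The mITT set with LOCF may also keep more than 25 per arm.
- *Patients from the first days after stroke are mixed with late outpatients.* The missing lower limit permits this, but no such case mix is described.
- *Every outcome is affected.* The acceptability questionnaire has no evident link to recovery stage.
- *The blocking should now be changed.* Recruitment and randomisation began on 22 October 2022 (Trial status), and the covariate serves the purpose without that.

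**Conclusion.** The point holds as a loss of precision, not as bias or an inflated type I error. The protocol allows any time up to six months, names no stratification factor and fixes unadjusted tests, so whatever prognostic effect time since stroke has is left as noise and uncorrected chance imbalance. How large that is cannot be read from the protocol; the power ranges depend on the assumed R² of 5–30% and on which scenario applies. If R² is close to zero, almost nothing is lost either way. The case for acting does not depend on settling this: adjustment gains precision whenever time since stroke is prognostic and costs almost nothing when it is not. It is a worthwhile, nearly free improvement. The planned sample size needs no correction on this account.

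**What to change.** Before database lock and unblinding, amend the Statistical analysis section as follows.

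1. Record days from stroke onset to randomisation for every patient. The date is needed for the eligibility check, so no new assessment is required.
2. Replace the unadjusted between-group test for the primary clinical outcome with a prespecified ANCOVA of week-4 HAMD-24 on arm, baseline HAMD-24 and days from stroke to randomisation. With baseline as a covariate, this gives the same treatment effect as modelling the change score, so it fits the primary outcome as defined in the Abstract.
3. Add the same time covariate to the between-arm models for NIHSS, MBI and MEP and to the SPM12 group models.
4. Leave the randomisation scheme as it is.

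The cost is about one degree of freedom per model for the time covariate, and a short analysis amendment. Patients, treatment, visits and sample size do not change.

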### Exclusion criteria

(1) Exclusion criteria for patients include the following:Have received other antidepressant therapy or involved in other clinical trials in the previous 2 weeks.Infarct located in the left DLPFC.Positive psychiatric history and major trauma exposure history, such as depression, epilepsy, etc., in the past.Other serious concomitant diseases (aphasia, severe edema, venous thrombosis, arteriosclerosis occlusion, diabetic vascular disease, peripheral neuropathy, spinal lesions, brain trauma, intracranial infection, brain tumors, etc.) or secondary diseases (heart, liver, renal failure, etc.).Infection around acupoints and/or intolerance to acupuncture manipulation.MRI or rTMS contraindications (claustrophobia, metal implants, cochlear implants, impulsator, etc.).(2) Exclusion criteria for healthy subjects include the following:Involved in other clinical trials in the previous 2 weeks.Positive psychiatric history and major trauma exposure history, including depression, epilepsy, etc., in the past.MRI or rTMS contraindications (claustrophobia, metal implants, cochlear implants, impulsator, etc.).

### Drop-out criteria

Low compliance and reluctantly continue to participate in the trial.Unsuitable to continue participation due to serious adverse reactions or complications during the study.Incompliance with standard treatments (less than 50% of The treatment times or receive other unrelated treatments) and/or MRI scanning or incomplete observation data affecting The assessment.

### Intervention

#### Initial therapy

During the 4-week study period, basic treatments for stroke such as antihypertensive agents, anticoagulants and antiplatelet agents, antidiabetic agents, and lipid-lowering drugs, will be allowed to be routinely received. Complication prevention (pressure ulcers and pneumonia) and nutritional support will also be allowed.

### Experimental group

The experimental group will be given EA and MRI-navigated rTMS treatment.

Firstly, EA treatment will be administered at the Neiguan (PC6, bilateral), Shuigou (GV26), Sanyinjiao (SP6, affected side), Yintang (EX-HN3), Shangxing (GV23), Baihui (GV20), and Sishencong (EX-HN1) acupoints. Disposable stainless-steel needles (0.25 mm × 40 mm; Huatuo brand, Suzhou Medical Supplies Factory Co., LTD., Suzhou City, China) will be used. The details of acupoint locations and related acupuncture manipulations have been listed in Figure 2 and Table 2. After skin disinfection, the acupuncturists will twist and thrust the needle handles to achieve the sensations of achiness, heaviness, and numbness (known as de qi) at all abovementioned acupoints. Following needle manipulations, EA instruments (SDZ-V, Hwato brand, Suzhou Medical Supplies Factory Co., Ltd., Suzhou City, China) will be used to attach the needle handles at EX-HN3, GV23, GV20, and EX-HN1, with a dilatational wave of 5 ~ 10 Hz and a current intensity of 1 ~ 3 mA depending on the patient’s tolerance. The needles will be removed after 30 min, except for GV26 without needle retention. Participants will receive 12 ~ 20 sessions over 4 weeks at a frequency of 3 ~ 5 times per week.

